## Abstract

**Background:**

Ventricular tachycardia (VT) is a life-threatening condition, which usually implies the need of an implantable cardioverter defibrillator in combination with antiarrhythmic drugs and catheter ablation. Stereotactic body radiotherapy (SBRT) represents a common form of therapy in oncology, which has emerged as a well-tolerated and promising alternative option for the treatment of refractory VT in patients with structural heart disease.

**Objective:**

In the STRA-MI-VT trial, we will investigate as primary endpoints safety and efficacy of SBRT for the treatment of recurrent VT in patients not eligible for catheter ablation. Secondary aim will be to evaluate SBRT effects on global mortality, changes in heart function, and in the quality of life during follow-up.

**Methods:**

This is a spontaneous, prospective, experimental (phase Ib/II), open-label study (NCT04066517); 15 patients with structural heart disease and intractable VT will be enrolled within a 2-year period. Advanced multimodal cardiac imaging preceding chest CT-simulation will serve to elaborate the treatment plan on different linear accelerators with target and organs-at-risk definition. SBRT will consist in a single radioablation session of 25 Gy. Follow-up will last up to 12 months.

**Conclusions:**

We test the hypothesis that SBRT reduces the VT burden in a safe and effective way, leading to an improvement in quality of life and survival. If the results will be favorable, radioablation will turn into a potential alternative option for selected patients with an indication to VT ablation, based on the opportunity to treat ventricular arrhythmogenic substrates in a convenient and less-invasive manner.

## Introduction

In patients with structural heart disease, catheter ablation by radiofrequency (RF) energy delivery is effective in the treatment of ventricular tachycardia (VT) recurrences, and is considered of pivotal importance in combination with implantable cardioverter defibrillator (ICD) and antiarrhythmic drugs to prevent sudden cardiac death [1–7]. However, results of RF cannot be extended to all patients with recurrent VTs; the possibility to effectively treat the arrhythmogenic substrate is indeed limited by several factors, including the complexity, extent, and depth of the arrhythmogenic substrate [8–11]. This evidence clearly explains the suboptimal percentage of patients successfully treated for VT. Moreover, the ablation procedure is complex, presents a high degree of invasiveness, and may expose the patient to several life-threatening complications; of note, in patients with severe cardiac dysfunction, and particularly in case of significant respiratory or renal comorbidities, the high procedural risk may even constitute by itself an absolute contraindication for any interventional or surgical approach [12].

The use of stereotactic body radiation therapy (SBRT, radioablation) represents a noninvasive approach, in which the energy delivery technique is not related to any cardiac catheterization [13, 14]. Advanced imaging techniques for the characterization of the substrate and the definition of the anatomical target are employed. This noninvasive approach minimizes the procedural risk associated with the insertion, positioning, and manipulation of the catheters, during both mapping and ablation. In this regard, radioablation allows the delivery of energy to any theoretical target in a three-dimensional system without the need for anatomical contact; furthermore, the prospect of simulating the lesion produced on the diagnostic model provides a patient’s “tailored” therapy, enhancing safety and effectiveness [15].

Of note, different cellular processes are involved in the mechanism of action of radioablation; the therapeutic effect of SBRT is supposed to arise basically from the induction of cellular death and transmural fibrosis that leads to the abolishment of abnormal conduction/automaticity in the myocardial tissue responsible of the arrhythmia [16, 17]. Fibrosis maturation is however progressive and requires several weeks to complete, so that in the intermediate phase, other factors, including acute inflammation and vascular injury, may impact on short-term outcome [16, 18].

Recently, SBRT has been used for the treatment of 35 patients with VT [13, 19–30]. SBRT, guided by imaging techniques partially integrated by electrocardiographic and/or electroanatomical data, significantly reduced in these patients the arrhythmic burden, in the absence of major adverse events correlated with the treatment applied.

Based on these evidences, we designed a spontaneous, prospective, experimental (phase Ib/II), open-label study to validate efficacy and safety of SBRT in a well-defined cohort of patients with recurrent VT not eligible to conventional catheter ablation.

## Methods

The STRA-MI-VT trial was designed as spontaneous, experimental (phase Ib/II), prospective, open-label study. Fifteen patients are expected to be enrolled. The design of the study is illustrated in Fig. 1 and in Table 1.

**Fig. 1 Fig1:**
[figure not shown]
Flowchart of STRA-MI-VT study. Legend: CT, computed tomography; ECG, electrocardiogram; OARs, organs at risk; QoL, quality of life; SBRT stereotactic body radiotherapy; VT ventricular tachycardia

**Table 1 Tab1:** Planning of the study activities

		Study phases							
		Screening and enrolment	Pre-treatment	Radioablation	Post-treatment (until discharge)	1 month FU	3 months FU	6 months FU	12 months FU
Study activities	Compliance with inclusion/exclusion criteria	X							
	Informed consent	X							
	Anamnesis		X						
	Physical examination		X		X				
	Laboratory tests		X		X				
	Thorax RX		X						
	Echocardiogram		X		X		X	X	X
	12-lead ECG		X		X		X	X	X
	ICD interrogation		X	X	X		X	X	X
	Other routine patient-related exams		X		X				
	QoL evaluation		X				X	X	X
	Cardiac CT		X						
	Electroanatomical mapping		X^*^						
	Simulation thorax CT and target and OARs definition		X						
	Treatment planning elaboration		X						
	Radioablation			X					
	Weekly phone contact					X			
	Cardiological visit				X		X	X	X
	Radiotherapy visit						X		X
	Thorax CT						X		X
	Adverse effects evaluation			X	X	X	X	X	X

^*^To be performed unless already in possess of necessary diagnostic information

*CT* computed tomography; *ECG* electrocardiogram; *FU* follow up; *ICD* implantable cardioverter defibrillator; *QoL* quality of life; *RX* radiography

### Study population

The population of the STRA-MI-VT study was defined following the inclusion/exclusion criteria reported below, which present an advantageous cost-benefit ratio in relation to the severity of patients’ arrhythmic condition.

#### Eligibility criteria

The inclusion criteria are as follows:Patients with relapsing VT (at least 3 episodes of VT conditioning ICD intervention or VT with incessant or similar-incessant presentation) that has proved to be refractory to any form of pharmacological or non-pharmacological treatmentPatients with contraindication to conventional ablation, in relation to the high risk associated with the procedure for the type/severity of the condition of heart disease and/or presence of severe comorbidity; or alternatively, patients who have already undergone RF ablation in presence of an arrhythmogenic substrate refractory to previous ablation procedures or not suitable for any interventional approach,^1^ refusing any surgical ablative attempt because of a proven high operative risk, in relation to the patient’s characteristicsEjection fraction of the left ventricle ≥ 20%Age ≥ 50 yearsICD/subcutaneous ICD recipientsSigned informed consent

The exclusion criteria are as follows:Inability to express informed consent to participate in the studyPrevious thoracic radiotherapy with cardiac involvementActive myocardial ischemiaCardiac revascularization < 120 days.Non-correctable hemodynamic instability (cardiogenic shock, New York Heart Association (NYHA) IV)Comorbidity with prognosis < 12 months or other contraindications deemed significantPregnant women

### Pre-treatment evaluation

Patients will preliminarily undergo the complete diagnostic workup defined for patients with an indication to conventional VT catheter ablation. In agreement with our ordinary practice, electroanatomical mapping (EAM) combined with cardiac computed tomography (CT) will represent the first choice of imaging to identify the arrhythmia substrate and to define the target area.

The patients’ quality of life will be evaluated using the Short Form-36 (SF-36) health questionnaire.

#### Cardiac computed tomography

Cardiac CT will be performed using a whole heart coverage (16 cm along Z-axis) CT scan (Revolution CT, GE Healthcare, Milwaukee, WI, USA) with the following parameters: slice configuration 256 × 0.625 mm, gantry rotation time 280 m s, and prospective electrocardiography (ECG) triggering. A new generation of iterative reconstruction, called ASIR-V (GE Healthcare), will be used for image reconstruction. Pre-scan sublingual nitrates and betablocker (i.v. metoprolol up to 20 mg) will be administered, if not contraindicated. Patients will receive a 1.5-mL/kg bolus of contrast medium (Iomeron 400 mg/mL, Bracco), divided in two separate bolus 5 mL/s followed by saline infusion, both at an infusion rate of 5 mL/s. A first CT scan will be obtained at the angiographic phase to have adequate coronary artery contrast opacification as routinely performed for coronary CT angiography. A second series of breath-hold and ECG-gated images will be acquired after 8 min from contrast agent injection (100 Kvp; 500 mA) for the detection of myocardial delayed enhancement (DE, Fig. 2, upper panel). Visual evaluation of DE will be performed and a narrow window width and level (350 W and 150 L) will be used for late scan evaluation that is best viewed as thick average intensity projections (0.5–0.8 cm). The presence of DE will be then confirmed as hyperdense myocardium with signal intensity > 2 standard deviation (SD) above remote myocardium, as previously described [31–33]. Myocardial wall thinning (wall thickness < 5 mm) and DE involving > 50% of myocardial thickness will be considered transmural DE. A dedicated post-processing reconstruction will be applied to extrapolate single DICOM files including only myocardial fibrosis volume, coronary and ascending aorta anatomy, pericardial fat volume, and selected extracardiac anatomical structure (i.e., spine and sternum).

**Fig. 2 Fig2:**
[figure not shown]
Diagnostic imaging obtained by cardiac CT combined with EAM to guide patient’s SBRT treatment. **Upper panel**: LV short axis view of cardiac CT scan obtained 8 min after iodinated contrast administration. Hyper-density on inferior and postero-lateral LV wall is well evident and represents transmural myocardial fibrosis with ischemic pattern extending from the base to the apex of LV. **Central panel**: High-density epicardial EAM combined with CT imaging. A large portion of the inferior wall is covered by diseased electrograms, with decreased amplitude (<< 1.0 mV, red-to-yellow in the “color-coded” map), as expression of an underlying electrical “dense scar.” In the same location, CT shows a pattern of discrete transmural fibrosis, thus perfectly matching the lesion revealed by EAM. **Lower panel**: The inferior panel shows the coverage (95% isodose) of the target volume obtained after optimization of treatment plan. The target volume is the result of imaging integration between simulation and diagnostic CT, and EAM. Legend: CT, computed tomography; EAM, electroanatomical mapping; LV left ventricle; SBRT stereotactic body radiotherapy

#### Electroanatomical mapping

A left ventricular (LV) endocardial electroanatomical mapping (EAM), which allows to reconstruct three-dimensional cardiac chambers and to detect intracardiac electrocardiogram, will be acquired with a conventional percutaneous approach. The standard for identifying major sites of arrhythmogenicity is represented by high-density EAM, acquired with the CARTO system (Biosense Webster), which provides essential information of voltage abnormalities, representing diseased tissue, and local activation times; as a rule, the LV map was consequently obtained by using Pentaray or Decanav catheter (Biosense Webster), acquiring a total of ≥ 500 points with more than 5 points/cm^2^ density in the areas of interest. Basically, the reference value of bipolar endocardial voltage to define diseased LV was 1.5 mV, being “dense scar” characterized by intracardiac electrogram (EGM) signals < 0.5 mV. With regard to the possibility to reveal any intramural/epicardial lesion, signals were considered pathological if signal amplitude was < 8.0 mV and/or < 1.0 mV for unipolar endocardial and bipolar epicardial electrograms, respectively.

Pre-acquired DICOM files will be then merged (imaging fusion) with EAM to characterize the VT substrate and validate the correlation between diseased myocardium diagnosed by EAM and fibrotic lesions revealed by CT (Fig. 2, central panel). This combined anatomical and functional characterization of the arrhythmia substrate will be used to identify areas of diseased myocardium responsible for the arrhythmias and will represent the target for SBRT. The evaluation will be performed by a panel of two electrophysiologists, one clinical cardiologist, one radiologist, and two radiotherapists, with more than 10 years of experience in their specific field, achieving a consensus on the target area.

Previous mapping and imaging integration data will be used for target identification only if acquired at the end of the last patient’s procedure, in order to ensure accuracy of substrate characterization. Eventually, it will be admitted to renounce EAM in selected patients with a contraindication to any interventional procedure in whom SBRT will be guided by imaging techniques only.

### Treatment

Patients will undergo a simulation CT (chest CT), acquired in order to include the whole lung fields (from the apex to the base), aimed at simulating the patient’s anatomy and allowing the correct positioning of the patient during the radioablation procedure. Subsequently, a series of CT scans will be acquired which include a free breathing CT and a “related breathing” CT (4D-CT) which provide information on respiratory movement. The information obtained by simulation CT, EAM, cardiac CT, and any other available imaging will be used to identify and draw: (1) both on free breathing CT and on 4D-CT, the ablation site represented by the clinical target volume (CTV) and (2) on the free breathing CT all surrounding anatomical structures, also known as organs at risk (OAR), including the ICD. The CTVs drawn on all the images of different respiratory phases will be transported on free breathing CT, and an internal target volume (ITV) will be defined as the union of the CTVs, taking into account the target respiratory motion. Starting from ITV, a planning target volume (PTV) will be built, expanding the ITV in three dimensions. This margin takes into account any residual uncertainty related to patient positioning, unwanted movements, and dose emission (Fig. 2, lower panel) [34]. The most appropriate physical-dosimetric study for the patient’s anatomy will be processed using treatment plan system (TPS) and will be generated in order to deliver a total dose of 25 Gy in a single fraction [14, 35], to achieve maximum coverage of the PTV region by minimizing the dose to the surrounding healthy tissues.

SBRT will be delivered using one of the linear accelerators installed at the IEO, i.e., 3 tomotherapy units, 1 Cyberknife, 1 Trilogy, and 1 Vero. All linear accelerators except Cyberknife will use a modulated intensity radiotherapy (IMRT) isocentric-based technique. In contrast, Cyberknife will deliver the treatment via non-isocentric beams, originated at arbitrary positions in the workspace and focused at arbitrary points in the target.

The choice of equipment to be used for each patient enrolled in the STRA-MI-VT study will be made taking into consideration different elements, such as size of the lesion to be treated, location of the lesion, patient anatomy, OARs near the lesion, presence of markers close to the lesion visible from the imaging systems, and concomitant pathologies [36]. The plan will be prepared simulating patient’s treatment on different linear accelerators to optimize the equipment for each specific case. All the linear accelerators are provided with image-guided radiotherapy (IGRT). The acquired images will be volumetric, i.e., cone-beam CT (CBCT) and/or fluoroscopic (kV), checking for both modes the accuracy of patient positioning before the delivery of the treatment dose.

### Pre-discharge evaluation

After SBRT, all patients will be continuously monitored by 12-lead ECG for a period of at least 5 days; routine laboratory tests and echocardiography examination will be provided within 24 h after SBRT and before hospital discharge. Particular care will be addressed to exclude secondary effects related to SBRT.

ICD interrogation will be performed immediately after SBRT and before patient discharge to verify device and lead parameters and exclude malfunctions. As a rule, ICD ventricular arrhythmias detection and therapies will be maintained the same as before SBRT. Furthermore, ICD remote monitoring will be set up for all patients.

### Follow-up

Adverse effects will be classified according to the international Common Terminology Criteria for Adverse Events v 5.0/CTCAE document.

A follow-up phone-call will be performed once a week for the first 4 weeks after SBRT.

Regular cardiological follow-up visits, including 12-lead ECG and ICD interrogation, will be performed 3, 6, and 12 months after SBRT. Echocardiography examination and SF-36 health questionnaire will be provided 3, 6, and 12 months after SBRT. Patients will be visited by a radiation oncologist, and thorax CT will be performed 3 and 12 months after SBRT.

Pharmacological therapy, including antiarrhythmic drugs, will be maintained the same as before SBRT during the entire follow-up.

With regard to the early post-SBRT phase and the possible occurrence of transient processes impacting on cardiac arrhythmogenicity, accordingly to literature [16–18, 21], a 6-week “blanking period,” starting immediately after SBRT treatment, will be considered in the analysis of VT recurrences during follow-up.

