### Endpoints of the study

#### Primary endpoints

Two primary endpoints of the study have been defined, represented by safety and efficacy of the treatment, respectively.Primary safety endpoint is to evaluate the safety of radiation therapy in the acute phase (during the first 30 days of the procedure) and at 3, 6, and 12 months. The incidence of serious adverse events related, or presumably related, to radioablation will be assessed as a percentage of the enrolled patients. Serious adverse events were the following:DeathCardio-circulatory arrestAcute myocardial infarctionCardiogenic shockPericarditis, myocarditis, and/or endocarditisAcute heart failureGastro-esophageal lesion (ulcer/stenosis/fistula/hemorrhage/perforation)Bronchopulmonary infectionInjury to the respiratory system (fistula/bronchial or tracheal stenosis, pulmonary fibrosis)Radio-induced oncogenesisPrimary efficacy endpoint is to evaluate the procedural effectiveness of therapy at 3, 6, and 12 months, represented by the total number of VT/VF episodes occurring after “blanking period,” compared with the period preceding the radioablation procedure (6 months).

VT episodes will be categorized as follows:VT episode > 30 s, regardless of the intervention of the ICDVT episode conditioning ICD intervention by means of “anti-tachycardia pacing” electrical therapy (without shock delivery)VT episode conditioning ICD shock intervention

The 6-week “blanking period” will start on the procedure day.

As a rule, pharmacological therapy, including antiarrhythmic drugs, will be maintained the same as before SBRT during the follow-up period. Changes of the pharmacological therapy will be determined only by specific clinical reasons.

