#### Calculation of the target sample size and statistical analysis

A sample of 15 patients will allow a 60% reduction in ventricular arrhythmic episodes to be assessed as significant (*p* < 0.05), assuming an average of 10 episodes in the 3 months preceding the procedure, with a statistical power of 90%. Continuous variables will be expressed as mean ± standard deviation or median and interquartile range variables with non-normal distribution, and discrete variables as absolute numbers and percentages. Primary efficacy endpoint (reduction of ventricular arrhythmic episodes) and secondary endpoints (clinical, echocardiographic, and psychometric characteristics) will be evaluated with the Student’s *t* test for paired data (continuous variables with normal distribution) or with the Wilcoxon sign rank test (variables with non-normal distribution). Kaplan-Meyer curves will be developed for event-free survival analysis at follow-up. All tests will be two-tailed and a *p* < 0.05 will be considered significant.

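### The 6-month baseline is not a period on unchanged background treatment, so a drug change or ablation late in it that altered the VT rate would be read as an SBRT effect

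*Protocol article*

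**What the plan says.** In the protocol article, the efficacy endpoint under Primary endpoints is the number of VT/VF episodes after the 6-week blanking period, "compared with the period preceding the radioablation procedure (6 months"). Under the sample size and statistical analysis heading, this is tested within patients by a paired t test or a Wilcoxon test. There is no concurrent control.

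Three places hold background treatment constant, all from SBRT onward:

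- Follow-up: "Pharmacological therapy, including antiarrhythmic drugs, will be maintained the same as before SBRT during the entire follow-up".
- Primary endpoints repeats the drug rule in softer form and adds: "Changes of the pharmacological therapy will be determined only by specific clinical reasons".
- Pre-discharge evaluation, on the device: "As a rule, ICD ventricular arrhythmias detection and therapies will be maintained the same as before SBRT".

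The eligibility criteria require VT that "has proved to be refractory to any form of pharmacological or non-pharmacological" treatment, and "at least 3 episodes of VT conditioning ICD intervention or VT with incessant or similar-incessant presentation". Neither carries a time window or a period of stable therapy. Previous ablation is admitted ("patients who have already undergone RF ablation in presence of an arrhythmogenic substrate refractory to previous ablation procedures") with no minimum interval before SBRT. Revascularisation is an exclusion only if it took place less than 120 days earlier, and no reference date is given for the 120 days.

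**The concern.** A before/after contrast isolates the effect of SBRT only if the rest of the treatment is alike on both sides. The stated rules fix the treatment on one side. A drug added four weeks before SBRT acts during about 15% of the baseline (4 of 26 weeks) and during all of follow-up, so most of its effect falls into the before/after difference. This happens even if the Follow-up rule is kept perfectly, so it is a different matter from drug changes made after SBRT.

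At stake is the main efficacy conclusion, which rests wholly on this contrast. Part of an observed reduction could belong to the last drug step or a recent ablation. If drugs were reduced or stopped late in the window, the error would run the other way and hide part of a real effect.

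**Working it through.** **Inputs from the protocol article.** Baseline 6 months, taken as 182.6 days or 26.09 weeks; 15 patients; 60% reduction from a mean of 10 episodes in 3 months; power 90%; two-sided 0.05. No SD is stated.

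**Assumptions.** The VT rate is otherwise stable, SBRT has no effect, and rates are per month. A drug step w weeks before SBRT multiplies the VT rate by r, with r = 0.7 or 0.5. The documents give no value for w, r or the share of patients affected.

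**1. The plan's own sizing.** "A sample of 15 patients will allow a 60% reduction in ventricular arrhythmic episodes to be assessed as significant" cannot be reproduced without an SD. Solving the paired t power function for a mean change of 6 (10 to 4), n = 15 and power 0.90 gives an SD of the paired change of 6.66. That value is used in step 3.

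**2. One affected patient.** With the early rate set to 1:

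- baseline B = (26.09 − w)/26.09 + r·w/26.09
- follow-up F = r
- apparent reduction = 1 − r/B

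For w = 4 and r = 0.7: B = 0.8467 + 0.7 × 0.1533 = 0.954, so the reduction is 1 − 0.7/0.954 = 26.6%. For r = 0.5: B = 0.923, so the reduction is 45.8%.

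| Weeks before SBRT | r = 0.7 | r = 0.5 |
|---|---|---|
| 2 | 28.4% | 48.0% |
| 4 | 26.6% | 45.8% |
| 8 | 22.9% | 40.9% |
| 13 | 17.7% | 33.4% |

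**3. The trial as a whole, one third affected, w = 4.** The cohort reduction is 1 − (s·r + 1 − s)/(s·B + 1 − s), with s = 1/3.

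- r = 0.7: 1 − 0.900/0.985 = 8.6%, or 0.86 of 10 episodes. With SD 6.66 and n = 15, P(p < 0.05) = 7.5%.
- r = 0.5: 1 − 0.833/0.974 = 14.5%, or 1.45 of 10 episodes, and P(p < 0.05) = 12.3%.

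**4. Cross-check by simulation with other assumptions.** Mean of 20 episodes in 6 months, between-patient CV 0.7, and a 50% drug effect from 30 days before SBRT in a quarter of patients. A significant result in favour of SBRT occurs in 6% to 15% of runs, depending on within-patient noise, against a nominal 2.5% in that direction.

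**5. Revascularisation.** If done on day 120, then (182.6 − 120)/182.6 = 34% of the baseline precedes it. With an earlier rate k times the later one, the false reduction in that patient is 1 − 1/(0.657 + 0.343k): 15% for k = 1.5 and 41% for k = 3 (k assumed). It falls to zero as the date approaches 183 days. In the simulation, a 30% effect at 120 days in a quarter of patients gives an apparent cohort reduction of about 3% and a favourable false-positive rate of 3% to 5%, against 2.5%.

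**The case against.** The refractoriness criterion is the best counter-argument. It selects patients whose drug steps failed, so a large lasting response to the last step cannot be common. This has weight. It makes a 30% to 50% effect in most of the cohort hard to reconcile with entry. It does not remove the problem, because VT can keep recurring at a lower rate after a drug step, the criterion has no time frame, and episodes before the step still count in the baseline.

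A second objection is that the text is a condensed article, and handling of baseline drug changes may be left to a full protocol or analysis plan. That is fair for the detail of the analysis. The comparator window, the constancy rules and the eligibility list, however, are all stated here, and the point concerns how they fit together.

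A reader might go further and infer that drug steps in the baseline are in fact being credited to SBRT, and always in its favour. The documents do not support this. They report no such steps, and drugs may equally be reduced or stopped before SBRT. A reader might also give revascularisation the same weight as drugs. It is minor, because at least 120 of about 183 baseline days follow the procedure, and fewer than 63 days are exposed if the 120 days run to enrolment and not to SBRT.

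Finally, a baseline restricted to the period after the last change is not safe as the primary analysis. With r = 0.5 and a step at 2 weeks, the plan's 10 episodes in 3 months leave 10 × (2/13.04) × 0.5 = 0.77 expected baseline episodes, so 46% of such patients would have none (Poisson, assumed). If VT clusters before SBRT, restriction can also make matters worse. Suppose the rate doubles in the last 4 weeks, with r = 0.7. The full baseline is then 0.847 + 1.4 × 0.153 = 1.061, and the apparent reduction is 34%. The restricted baseline is 1.4, and the apparent reduction is 50%. This objection stands and shapes the fix.

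**Conclusion.** The point holds in conditional form. Nothing in the article makes the 6-month baseline a period on the regimen carried into follow-up. A change late in that window that altered the VT rate would therefore be counted as SBRT effect, in whichever direction it acted. Under the assumed drug effect of 30% to 50% from 4 weeks before SBRT, the error is 27% to 46% in an affected patient. The false-positive rate is about 7.5% to 12% with one third of patients affected. These sizes depend on the assumed effect, timing and share, and on the SD of 6.66 implied by the sizing. Antiarrhythmic drugs are the main instance. A recent RF ablation works in the same way and has no minimum interval. Revascularisation 120 to 183 days before SBRT is a smaller, secondary instance.

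The bias alone does not explain a reduction of the planned size: even with every patient affected, a 50% drug effect at 4 weeks gives 46%, short of 60%. It limits what may be attributed to SBRT.

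**What to change.** Keep the 6-month baseline as the primary comparison, with baseline and follow-up both expressed as episodes per month. Then:

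1. Record the dates of antiarrhythmic drug starts, stops and dose changes, RF ablation and revascularisation in the 6 months before SBRT.
2. Prespecify a sensitivity analysis in which each patient's baseline starts at the last such change, in any direction, with a stated minimum baseline length. Alternatively, exclude from it patients with a change in the window.
3. State that the reduction will be attributed to SBRT on unchanged background only if this analysis agrees with the primary one.
4. Reconcile the absolute drug rule under Follow-up with the qualified one under Primary endpoints, so that the reader knows what constancy after SBRT means.

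The cost is a paragraph of text and some data collection. Table 1 schedules an anamnesis and a device interrogation before treatment but does not show that dated drug changes are captured, so a data field may be needed. Affected patients will have shorter and noisier baselines, and the restricted estimate may itself be distorted by VT clustering before SBRT. No change to treatment or eligibility is proposed.
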